### Participant Timeline

Patients will be randomly allocated to the intervention or control group in a 1:1 allocation ratio. The enrollment will last up to the achievement of the sample size. The most important time points for the assessment of pain development are 3 and 6 months poststroke, with the addition of measurement time points in the subacute phase (29, 34). In fact, differences in motor activity of paretic limbs 24–36 h after symptoms onset, and also at 3 and 6 months (35, 36) have been demonstrated. Therefore, the assessment of the primary and secondary outcomes will be conducted at the following time points: baseline measurement at Sant'Anna Institute admission (24–72 h since stroke event) (*t*_0_); 1 month after stroke (*t*_1_), i.e., at half of the rehabilitation period; 2 months after stroke (*t*_2_), i.e., after the completion of neurorehabilitation with ARAMIS in the intervention group and of conventional rehabilitation in the nonintervention group; 3 months (*t*_3_) and 6 months (*t*_4_) after stroke, since the latter are critical for rehabilitation and pain development. Routine clinical and neurophysiological assessments will be performed before and at the end of the treatment. Loss of tolerance to the procedure up to discontinuation will be recorded on a specific form. The schedule of enrollment, interventions, and assessments is reported in Table 1.

**Table 1 T1:** Schedule of enrollment, interventions and assessments according to Standard Protocol Items: Recommendations for Interventional Trials (SPIRIT).

	**Study period**					
	**Enrolment**	**Allocation**	**Post-allocation**			
**Timepoint**	** *–t_**1**_* **	**0**	** *t_**1**_* **	** *t_**2**_* **	** *t_**3**_* **	** *t_**4**_* **
**Enrolment**						
Eligibility screen	X					
Informed consent	X					
Physical examination	X					
Allocation		X				
**Interventions**						
*ARAMIS*			X	X		
Conventional neurorehabilitation			X	X		
**Assessments**						
Primary endpoint variables		X				
Secondary endpoint variables		X				
Assessment of activation volume			X	X		
FAI		X				X

### Sample Size

The calculation of the sample power is based on literature data (25, 36–40) to obtain 25% of improvement in the primary endpoint using G^*^Power 3.1.9.7 (41). The formula for calculating the sample size is given, for two arms of the same size, as it follows:

$$\begin{array}{l} n=\left[{\left(Z_{\alpha /2}+Z_{\beta }\right)}^{2}\times \left(2{\left(\sigma \right)}^{2}\right)\right]/{\left(\mu 1-\mu 2\right)}^{2} \end{array}$$

where,

*n* = sample size required in each group;

*Z*_α/2_ = 1.96, according to 5% level of significance;

*Z*_β_ = 0.84 for 80% power;

σ = standard deviation;

μ1 – μ2 = primary outcome measures significant difference = 6.34 with ARAMIS and 5.4 with conventional rehabilitation (25);

*d* = 0.3.

Therefore, considering a 95% confidence level and a study power of 80% (42), the result will be *n* = 53 per arm.

Adjusted sample size *n*_1_ to account for potential drop-out rates is *n*_1_ = *n*/(1–*d*), where *d* = 10% (43), thus *n*_1_ = 118 patients will be recruited, 59 per each arm.

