## Introduction

### Background and Rationale

Stroke represents one of the most serious causes of death and disability-adjusted life-years lost (1) destined to keep increasing due to global aging. One of the most common long-term disabilities occurring in over 69% of cerebrovascular lesions consists of impaired motor function of the upper extremities up to hemiplegia in the following 5 years in 56% of cases (2, 3). Stroke is complicated by the occurrence of poststroke pain usually within 6 months from the acute event (4), with poststroke pain syndromes reported in up to 30%−40% of stroke outliving patients (5), chronic in 11–55% of patients (6). The latter include pain caused by different pathophysiology in which nociceptive and neuropathic features can coexist ranging from pain secondary to spasticity, shoulder pain, complex regional pain syndrome (CRPS), and headache, in 1 out of 10 stroke sufferers, that is, migraine-like in 31.3% cases (7), to central poststroke pain (8). Shoulder pain is the most frequent affecting some 30–40% of stroke survivors (6). Lenticulocapsular strokes can cause hemiparesis with consequent shoulder pain (9). The development of poststroke pain correlates to the severity of stroke and paresis is associated with a 3.1-fold higher risk for stroke-related pain (10). Unfortunately, often patients suffering from pain after stroke do not find relief in current analgesic treatment because it is not supported by clinical trials, as a consequence, guidelines are lacking (9). In fact, the systematic review and meta-analysis of literature has highlighted that very few clinical trials assess the efficacy of opioids, the most potent analgesics on poststroke pain, the number of patients is very small and these studies have not been designed specifically for this condition, thus usually not evaluating the correlation between rehabilitation, pain, and physical functioning after stroke (11). Actually, stroke survivors do not even benefit from clinical trials on the novel preventative treatment of migraine, e.g., the anticalcitonin gene-related peptide monoclonal antibody eptinezumab that can provide rapid and longer-lasting action (12). This is often due to the lack of use of pain scales for an objective pain assessment validated in specific populations, e.g., patients affected by stroke, and this problem becomes even more worrying for patients with aphasia and noncommunicative and in the pandemic emergency (13–16). Robot-assisted neurorehabilitation for patients with stroke having the Integrated Robotic System for Stroke (IRSS) prototype Automatic Recovery Arm Motility Integrated System (ARAMIS) has provided a significant improvement of motor recovery (17). It consists of two computer-controlled, symmetric, and interacting exoskeletons that impress to the paretic arm the same strength and movement of the healthy arm and it has been validated in stroke survivors. The rationale for the use of ARAMIS in poststroke neurorehabilitation of the paretic upper limb relies on the possible prevention of aberrant early plasticity. According to our working hypothesis, ARAMIS might improve plasticity in agreement with the concept underlying the Reinforcement-Induced Movement Therapy (18), avoiding the occurrence of spasticity and hypotonia.

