### Eligibility Criteria

Consecutive patients, admitted to Sant' Anna Institute with the diagnosis of stroke after hospital discharge will be enrolled, accordingly with the following inclusion criteria:

- First-ever stroke within 24–72 h from diagnosis confirmed through functional MRI scan, regardless of the side, location, and extension of the lesion;-Stroke-related hemiplegic patients of any age at hospital discharge within 48–72 h after stroke with fMRI scan of the area affected;-Severe upper limb impairment, according to the Upper Extremity Subscale of the Fugl–Meyer Motor Assessment [FMA-UE (0-35) (21)];-Absence of hemiplegic upper limb-related baseline pain based on the visual analog scale (VAS), the bedside active examination with a numerical rating and, also, the douleur neuropathique en 4 questions (DN4) for the evaluation of neuropathic prestroke pain.

Exclusion criteria will be:

-Bilateral impairment;-Presence of aphasia;-Presence of cognitive impairment, as assessed using the cognitive assessment scale for patients with stroke (22), to avoid interference of aphasia or hemispatial neglect that may occur with the commonly used Mini-Mental State Examination (23) and Montreal Cognitive Assessment (24);-Stroke diagnosis without the occurrence of hemiparesis of the upper limb;-Previous rehabilitation.

Due to the lack of specific observational tools for poststroke pain in noncommunicative patients, this pilot study will not include patients affected by aphasia and cognitive impairment. The informed consent will be obtained by healthcare operators and patients will be informed about the study and they will be provided with a consent form. No additional consent provisions for biological specimens will be needed since the latter will not be collected.

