### Outcomes

The effect of robot-assisted rehabilitation using ARAMIS on the prevention of the development of poststroke pain is the primary endpoint of the ROBOCOP study. The primary outcome measures consist in the assessment of pain through the VAS, including a bedside active examination and probing of somatosensory functions to test touch, temperature, and pain sensations (26). The development of neuropathic components of poststroke pain will be assessed using the DN4. The secondary endpoints include spasticity, tightly linked to pain and developed by up to 40% of patients with hemiparetic stroke, and clinical motor rehabilitation. Spasticity will be assessed using the Modified Ashworth Scale (MAS) (27) and the Resistance to Passive movement Scale (REPAS), based on the Ashworth scale (28), for major joint movements in upper and lower limbs. Clinical motor rehabilitation will be measured according to the Standardizing Measurement in Arm Rehabilitation Trials [SMART] toolbox of the recommended core set of outcome measures for rehabilitation after stroke (29, 30). The latter includes FMA-UE, the Action Research Arm Test, and the activities of daily living/stroke-specific outcomes of the Barthel Index. The clinical motor rehabilitation will also be characterized through structural and functional MRI scan. In particular, structural MRI is intended to evaluate infarct and injury volume (31) and functional MRI to assess the activation volume in the stroke ipsilateral hemisphere during movement of paretic limb, which is related to the extent of behavioral recovery (32). The connection strength between the ipsilesional primary motor cortex and the contralateral regions will be examined (33).

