## Discussion

Cerebrovascular accidents are often accompanied by motor disability and chronic pain. Poststroke pain consists of complex syndromes including both nociceptive musculoskeletal and neuropathic features (49). Due to its characteristics, poststroke pain is often underdiagnosed and unrelieved (50). The best management option for chronic pain consists of its prevention. To this aim, this is the first clinical trial to study the use of an IRSS in subacute neurorehabilitation after stroke. In particular, ARAMIS has provided more efficacy than conventional poststroke neurorehabilitation when applied for 7–8 weeks in the improvement of motor function and activities of daily living (17, 25, 51, 52). When the lesion is high after lateral medullary infarction, known as Wallenberg's syndrome, or in the ventroposterior part of the thalamus, central poststroke pain ensues (6). In the event hemiparesis occurs, the healthy arm may offset the effect of spasticity and locomotion (52, 53). Within this frame, ARAMIS may prevent central pain, and, concurrently, may drive correct re-organization in hemiplegic patients capturing the motions and the strength of the unaffected upper limb. In fact, ARAMIS consists of two exoskeletons with 6 degrees of freedom driven by two engines and controlling the shoulder joints to compensate for the inadequate motility and strength of the paretic arm (51). Robot-assisted motor rehabilitation and myoelectrical stimulation are demonstrated to provide reduction of the upper limb impairment (38, 39, 54–56) and pain improvement (40, 57, 58). Also, actigraphic measure systems can predict acute phase stroke prognosis (59), supporting the role of technological progress in stroke. Furthermore, the use of these devices can help the familiarization of poststroke survivors with the latter technology (60). However, a decrease in upper limb impairment does not always correlate to practical and daily functional improvement and this translational aspect needs to be studied for effective neurorehabilitation (61). In fact, the wide multicenter trial for the evaluation of robot-assisted training for the upper limb after stroke (RATULS) has demonstrated that robotic neurorehabilitation does not significantly improve the upper limb function (62). Pain intensity has been positively correlated with time since stroke and negatively with motor function (44), supporting the need to examine the role of robot-assisted rehabilitation in pain processing and to clear the mechanisms necessary for effective functional gain. The latter is a top ten priority for stroke survivors (63). Therefore, the role of ARAMIS-assisted neurorehabilitation in the prevention of poststroke pain occurring 3–6 months after stroke deserves investigation. The efficacy of robot-assisted neurorehabilitation in the prevention of chronic poststroke pain could pose the basis for a remarkable improvement of stroke sufferers' quality of life. Moreover, a better and deeper understanding of robot-related motor learning is needed (55) and, although the stage is a predictor for better rehabilitation outcomes, IRSS neurorehabilitation, without significant differences among the several devices existing (64), has proven promising results also in chronic stroke survivors (65). In this already fragile population, robot-assisted rehabilitation may also reduce the use of analgesics known to be endowed with serious side effects. In fact, fragile populations are often subjected to limited and inappropriate pain treatment (66–68). The next step will consist in investigating the effect of this neurorehabilitation procedure on the use of analgesics, both synthetic and of natural origin, as the essential oil of bergamot endowed with analgesic (69) and flumazenil insensitive anxiolytic-like (70) properties and which has been engineered allowing double-blind clinical trials (71, 72).

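### The two means behind the sample size (6.34 and 5.4) fit no reading of the pain endpoint, so the stated 80% is not shown to be power for preventing poststroke pain

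*Protocol article*

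**What the plan says.** All places are in the protocol article.

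- **Outcomes:** "prevention of the development of poststroke pain is the primary endpoint of the ROBOCOP study", and "The primary outcome measures consist in the assessment of pain through the VAS". The DN4 covers neuropathic components.
- **Eligibility Criteria:** patients must show "Absence of hemiplegic upper limb-related baseline pain based on the visual analog scale (VAS") and on further bedside testing.
- **Sample Size:** the target is a 25% improvement in the primary endpoint. The formula is the usual one for comparing two means, with Z values "1.96, according to 5% level of significance" and "0.84 for 80% power". The effect is "primary outcome measures significant difference = 6.34 with ARAMIS and 5.4 with conventional rehabilitation", taken from reference 25. The SD appears as a symbol without a value, followed by d = 0.3 without a definition. The result is 53 per arm. A second d, now 10% dropout, brings it to 59 per arm and 118 in total.
- **Statistical Analysis:** pain at 3 and 6 months against baseline is summarised by means and standard errors and tested by t-test or Mann–Whitney, with a linear mixed model over time.
- **Discussion:** reference 25 is among the sources cited for the benefit of ARAMIS "in the improvement of motor function and activities of daily living (17, 25, 51, 52"). Pain improvement is cited to references 40, 57 and 58.
- **Objectives and Trial Design:** the study is called a pilot and exploratory.

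**The concern.** The article labels the two means as the primary outcome, and the primary outcome is pain. Lower pain is the benefit, yet the ARAMIS value is the higher one. Enrolled patients have no arm pain to lose, so the values cannot be reductions from baseline either. If the means belong to another kind of scale, the trial's only size justification says nothing about its primary endpoint.

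This affects how the result will be read. With a claimed 80% power, a null finding would be taken as evidence against a pain benefit. If that power was calculated for a motor gain, the inference has no basis.

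**Working it through.** **Inputs.** From Sample Size: Z = 1.96 and 0.84; means 6.34 and 5.4; target 25%; d = 0.3; n = 53; dropout 10%. From Background and Rationale, used only for illustration: poststroke pain in up to 30–40% of survivors. Every SD and every arm-specific pain rate below is an assumption, because the article gives none.

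**1. Can the stated figure be reproduced?**
Formula: n = (1.96 + 0.84)² × 2σ² / (μ1 − μ2)².
- (1.96 + 0.84)² × 2 = 7.84 × 2 = 15.68.
- μ1 − μ2 = 6.34 − 5.4 = 0.94; squared, 0.8836.
- Solving for σ at n = 53: σ = √(53 × 0.8836 / 15.68) = √2.987 = 1.73, a standardised effect of 0.94 / 1.73 = 0.54. Neither figure is stated.
- d = 0.3 as the standardised effect: n = 15.68 / 0.09 = 174.2, so 175 per arm. With 53 per arm, power would be 34%.
- d = 0.3 as the SD: n = 15.68 × 0.09 / 0.8836 = 1.6, so 2 per arm.
- Dropout step: 53 / 0.9 = 58.9, so 59 per arm and 118 in total. Only this step reproduces.

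**2. Do the means match the 25% target?**
0.94 / 5.4 = 17.4%, and 0.94 / 6.34 = 14.8%. A 25% change from 5.4 would be 1.35.

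**3. Can the means be pain?**

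| Reading of 6.34 vs 5.4 | Consequence |
|---|---|
| Pain level or frequency | ARAMIS is worse by 0.94 |
| Pain reduction from baseline | Not possible: no arm pain at entry |
| A scale where higher is better | The sign fits, but the scale is not the pain endpoint |

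**4. What could 53 per arm deliver for pain?** Two-sided 5%, normal approximation.

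(a) Difference of 0.94 VAS points, power = Φ(0.94 / (σ√(2/53)) − 1.96):

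| Assumed SD | 0.94 / (σ√(2/53)) | Power |
|---|---|---|
| 2 | 2.42 | 68% |
| 2.5 | 1.94 | 49% |
| 3 | 1.61 | 36% |

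(b) and (c) Pain as yes/no, comparing two proportions p1 and p2 with mean p̄: power = Φ((p1 − p2 − 1.96 × √(2p̄(1 − p̄)/53)) / √((p1(1 − p1) + p2(1 − p2))/53)).

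| Control rate | (b) 25% relative fall | Power | (c) 25-point fall | Power |
|---|---|---|---|---|
| 30% | to 22.5% | 14% | to 5% | 93% |
| 35% | to 26.25% | 16% | to 10% | 88% |
| 40% | to 30% | 19% | to 15% | 83% |

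The stated inputs do not select among these rows.

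**The case against.** Several points on the other side have force.

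- **The direction does not change n.** The formula squares the difference and the test is two-sided. This stands: the sign is evidence that the inputs belong to another outcome, not an arithmetical error in 53.
- **The source is not at hand.** That the means are motor scores is inferred from how the Discussion cites reference 25. The Sample Size section also lists references 36–40, and the Discussion cites reference 40 for pain; what it contributed cannot be seen. The motor reading therefore stays a probability. The main point does not need it, because the pain readings fail on the article's own terms.
- **An article may leave an SD to the full protocol.** An absent SD alone would not be a finding. Here the inputs that are printed (0.94, 25%, d = 0.3, n = 53) do not agree with one another.
- **The study is a pilot.** True, but it still claims 80% power and a target improvement in its primary endpoint.

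A reader might go further in two directions that the document does not support.

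- *That the trial has only 14–19% power.* This requires the 25% to be a relative fall in a yes/no pain outcome. The article says neither, and it plans to compare means. Read as 25 percentage points, power is 93–83%.
- *That means of 5.4 and 6.34 are impossible on a 0–10 VAS.* With 30–40% affected, the mean cannot exceed 3–4. But one supporting sentence, "Shoulder pain is the most frequent affecting some 30–40% of stroke survivors (6"), concerns shoulder pain only. The same section gives chronic pain in up to 55% and a 3.1-fold higher risk with paresis, and the trial enrols hemiplegic patients. At 55% the ceiling is 5.5, which is above 5.4. Such means are implausible, not proven unattainable.

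**Conclusion.** The concern holds in this form: the 80% is not shown to be power for preventing pain, and the true power for pain cannot be derived from the article. It may lie above or below 80%. Under the illustrations it ranges from 14% to 93%, and the width of that range reflects what the paragraph leaves open: the scale, the SD, the control value, and whether the 25% is relative or absolute.

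Two parts need no outside assumption: no pain reading of 6.34 against 5.4 fits the endpoint and the entry criteria, and the printed inputs contradict the stated 25% and do not yield 53. The motor or functional origin of the means is probable only. The document does not establish that the sample of 118 is too small.

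**What to change.** Keep 118 patients and rewrite the Sample Size paragraph:

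1. Withdraw the 80% claim for pain that rests on 6.34 and 5.4.
2. State the power, or the detectable difference, of 53 evaluable patients per arm for pain as the Statistical Analysis section compares it: VAS at 3 and 6 months. Give the assumed control value, the SD, an effect in the direction of less pain with ARAMIS, and whether the 25% is relative or absolute. If no pain data exist, give a range over plausible SDs.
3. Name the scale of 6.34 and 5.4. If it is a motor score, present it as the power basis for that secondary endpoint, with its SD.
4. Define d = 0.3 or remove it, and use a different symbol for dropout.
5. Word the pain conclusion as exploratory, in line with Objectives and Trial Design.

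The paragraph should not introduce a new yes/no pain endpoint with effects worked back from 53 and presented as the target. That would also change Outcomes and Statistical Analysis, and would justify the effect by the size already chosen.

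The cost is one paragraph and no additional patients. The downside is a power statement for pain that will probably look less favourable.

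### Sample Size: d = 0.3, 53 patients per arm and 80% power cannot all be true under the printed formula

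*Protocol article*

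**What the plan says.** The Sample Size section of the protocol article says that the calculation was made "to obtain 25% of improvement in the primary endpoint using" G*Power. It prints the usual normal-approximation formula for comparing two means with equal arms. The listed inputs are:

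- Z values of 1.96 (5% significance) and 0.84 (80% power).
- An SD that is named but given no value: "σ = standard deviation".
- The two means: "primary outcome measures significant difference = 6.34 with ARAMIS and 5.4 with conventional rehabilitation".
- A last entry, d = 0.3, with no description.

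The conclusion follows directly: "Therefore, considering a 95% confidence level and a study power of 80% (42), the result will be *n* = 53 per arm". The letter d is then used again, this time defined as a drop-out rate of 10%, to reach 59 per arm and 118 in total. The Statistical Analysis section plans an independent t-test, or a Mann–Whitney U test for skewed data, with significance at p < 0.05.

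**The concern.** The size of the trial and its claim of 80% power both rest on this one paragraph, and the figure of 53 does not follow from what is printed above it. In a list of inputs for a G*Power two-group comparison, d = 0.3 would ordinarily be read as the standardised difference, and an effect of that size needs far more than 53 per arm.

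As the paragraph stands, a reader cannot tell what effect the trial is able to detect. If 0.3 is the effect the investigators expect, the trial would miss it about two times in three, and a null result could be taken as evidence that robot-assisted rehabilitation does not prevent pain.

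**Working it through.** **Inputs (all from Sample Size).** Z values 1.96 and 0.84; difference 6.34 − 5.4 = 0.94; SD not printed; d = 0.3, unlabelled; n = 53 per arm; drop-out 10%.

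**Formula.** n per arm = (1.96 + 0.84)² × 2σ² / (μ1 − μ2)² = 15.68 × σ² / (μ1 − μ2)². With d = (μ1 − μ2)/σ this is 15.68 / d².

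**1. The plan's own figures.** The drop-out step reproduces: 53 / 0.9 = 58.9, so 59 per arm and 118 in total. The step to 53 does not, whichever meaning is given to 0.3:

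| Reading of 0.3 | Calculation | Result per arm | Printed |
|---|---|---|---|
| Standardised difference | 15.68 / 0.09 = 174.2 | 175 (176 by noncentral t) | 53 |
| SD | 15.68 × 0.09 / 0.94² = 1.6 | 2 | 53 |
| Drop-out | 53 / 0.7 = 75.7 | 76 | 59 |

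The drop-out reading also contradicts the 10% given a few lines later. Keeping 0.3 as the standardised difference and changing the test does not help: a one-sided test needs 138 to 139 per arm, and a two-sided Mann–Whitney test about 184.

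**2. Power if d = 0.3 is the standardised difference.** For a two-sided 5% t-test, power is 33.4% with 53 per arm. With all 59 per arm evaluable it is 36.6%. The normal approximation gives 33.9% and 37.0%.

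**3. What would produce 53.** Solving the printed formula for the SD with a difference of 0.94:

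σ = √(53 × 0.94² / 15.68) = √(46.83 / 15.68) = 1.73, so d = 0.94 / 1.73 = 0.54.

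By the t-test, 53 per arm has 80% power at d = 0.549, which corresponds to σ = 0.94 / 0.549 = 1.71. By contrast, d = 0.3 with the same difference implies σ = 0.94 / 0.3 = 3.13. One SD cannot serve both.

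Because no SD is printed, the table below shows how n depends on it for a difference of 0.94 (normal formula, unrounded Z values; each SD is an assumption):

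| Assumed SD | n per arm |
|---|---|
| 1.5 | 40 |
| 1.7 | 52 |
| 1.75 | 55 |
| 2.0 | 72 |
| 2.5 | 112 |
| 3.13 | 175 |

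**4. The 25%.** 0.94 / 5.4 = 17.4% and 0.94 / 6.34 = 14.8%. Neither ratio of the printed means is 25%.

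**The case against.** The strongest reply is that d = 0.3 is never called an effect size. The printed formula contains no d, and the only meaning the article gives that letter in words is drop-out. If the investigators used the 0.94 difference with an SD near 1.7, then 53 is right, the trial has its 80% power on its own assumptions, and 0.3 is a stray entry. This stands. A reader might infer that the trial is simply underpowered, with 33% power on its own stated effect; the article does not support that without the condition that 0.3 is the standardised difference.

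A reader might also combine a 25% improvement on 5.4 (a difference of 1.35) with an SD of 1.73 and say that the stated inputs imply yet another sample size. That does not hold. The SD is not stated; it was obtained by working back from 53, so any size derived from it is circular. Nor does the article say what the 25% is a percentage of, so the mismatch with 17.4% is a lack of reconciliation and not a proven error.

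Two further points are fair. The article condenses a fuller protocol, so the absence of an SD value is not in itself a fault. And the trial is called a pilot (Objectives, Eligibility Criteria) and exploratory (Trial Design), which softens the consequence of a null result. Neither removes the contradiction. An SD of about 1.7 in the full protocol would rescue 53 but make the printed 0.3 wrong, and a trial that claims 80% power and tests at p < 0.05 needs a power statement that can be reproduced.

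**Conclusion.** The paragraph is wrong as written: under the printed formula, d = 0.3, 53 per arm and 80% power cannot all stand. Which entry is wrong cannot be settled from the article.

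- If 0.3 is the standardised difference, the requirement is 175 to 176 per arm and power at 53 is about 33%. Its place among the inputs, the use of G*Power and the separate 10% drop-out make this the natural reading, but it remains an inference.
- If 53 is right, d is about 0.54 to 0.55, the SD behind it about 1.71 to 1.73, and 0.3 is a wrong entry. That SD is also an inference.

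The double use of d is a matter of notation and does not affect the step from 53 to 59. All figures assume a two-sided 5% test and equal arms, as printed.

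**What to change.** Keep 118 patients and rewrite the sample-size paragraph so that it can be reproduced:

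1. State the SD actually used, its source and the outcome scale to which 6.34, 5.4 and the SD belong. An SD worked back from 53 should not be written in as if it had been an input.
2. Say what d = 0.3 is, correct it, or delete it.
3. Say what the 25% is a percentage of, or replace it.
4. Use a symbol other than d for drop-out.
5. Report what the design can detect: 53 evaluable patients per arm give 80% power (two-sided 5% t-test) for a standardised difference of about 0.55. If 0.3 is the effect intended, state that power for it is about 33%.

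The cost is one reworded paragraph and possibly a less favourable stated power. No additional patients are needed for this change.

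### The printed sample-size inputs do not support 53 per arm at 80% power: σ has no value, and the undefined d = 0.3 does not fit as a standardised difference

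*Protocol article*

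**What the plan says.** All of this stands in the protocol article, Methods, Sample Size.

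- The formula, given "for two arms of the same size", is n = (Zα/2 + Zβ)² × 2σ² / (μ1 − μ2)² per group.
- The Z values are "1.96, according to 5% level of significance" and "0.84 for 80% power".
- The effect is given as "primary outcome measures significant difference = 6.34 with ARAMIS and 5.4 with conventional rehabilitation (25"), a raw difference of 0.94.
- The dispersion is given only as "σ = standard deviation", with no number.
- The last input is d = 0.3. It has no definition, and the printed formula contains no d.
- The conclusion is "considering a 95% confidence level and a study power of 80% (42), the result will be" n = 53 per arm.
- The line beginning "Adjusted sample size" then uses d again, now as a 10% drop-out rate in n/(1 − d), and reaches 59 per arm, 118 in total.

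The section also says that the calculation was made in G*Power, "to obtain 25% of improvement in the primary endpoint using" that program.

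**The concern.** The article prints a formula, its inputs, the result and a power claim, so a reader should be able to get from one to the other. Here that is not possible. The formula needs σ, which has no value. The one number that could stand in for it, d = 0.3, carries the usual symbol for a standardised difference, but under that meaning it leads to a sample size more than three times the stated one.

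At stake is what the trial can detect. A standardised difference of 0.3 and one of about 0.55 imply standard deviations that differ by a factor of about 1.8 for the same raw difference (3.13 against about 1.72). If the result is null, a reader needs to know whether the trial had four chances in five, or about one in three, of detecting the difference it was planned around. The paragraph does not say which.

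**Working it through.** **Inputs** (all from the Sample Size section): Zα/2 = 1.96; Zβ = 0.84; μ1 − μ2 = 6.34 − 5.4 = 0.94; d = 0.3, undefined; σ not given; drop-out 10%.

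**Formula in terms of the standardised difference.** With δ = (μ1 − μ2)/σ, the printed formula is n = 2(Zα/2 + Zβ)²/δ². The numerator is 2 × (1.96 + 0.84)² = 2 × 7.84 = 15.68.

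**Attempt to reproduce 53.**
- δ = 0.3, squared as the formula requires: 15.68/0.09 = 174.2, so 175 per arm (176 by the t-test). Not 53.
- 0.3 entered unsquared: 15.68/0.3 = 52.27, so 53. This matches.
- Other uses of 0.3 do not give 53: one-sided test, 138 or 139 per arm; paired or one-sample test, 90; analysis of variance with f = 0.3, about 90 in total; Mann–Whitney, about 184 per arm; 0.3 as the standard deviation, 2 per arm; 0.3 as the variance, 6 per arm.

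**Back-solving for σ without using d.** A result that rounds up to 53 lies above 52 and at most at 53.
- n = 53: δ = √(15.68/53) = 0.544, σ = 0.94/0.544 = 1.73.
- n = 52: δ = √(15.68/52) = 0.549, σ = 0.94/0.549 = 1.71.

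So an unprinted σ of about 1.71 to 1.73 gives 53 at 80% power with the squaring done correctly. A t-test calculation of the kind G*Power makes, at δ = 0.55, gives 52.9, also 53. In this range δ² runs from 0.544² = 0.296 to 0.549² = 0.302, which is about 0.3. By contrast, δ = 0.3 would need σ = 0.94/0.3 = 3.13.

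**Power if δ = 0.3** (normal approximation, Φ(δ√(n/2) − 1.96)):

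| Per arm | Normal approximation | t-test |
|---|---|---|
| 53 | Φ(0.3 × √26.5 − 1.96) = Φ(−0.416) = 33.9% | 33.4% |
| 59 | Φ(0.3 × √29.5 − 1.96) = Φ(−0.331) = 37.0% | 36.6% |

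**Drop-out step.** 53/(1 − 0.10) = 58.9, so 59 per arm and 118 in total. This reproduces. The value 0.3 was not used as the drop-out rate, since 53/0.7 = 75.7 would give 76 per arm.

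**The case against.** The strongest reply is that the formula contains σ and a mean difference, not d, and that the article does print an effect: 0.94. With a standard deviation near 1.72, 53 per arm at 80% power is correct. The source cited for the means is not at hand, so such a value cannot be ruled out. On that view the sample size is sound, and the defect is a missing σ and a wrong or stray label.

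This stands, and it limits the point. A reader might infer that the authors forgot to square 0.3, or that the trial simply has 34% power. The article supports neither as fact. It never calls 0.3 a standardised difference, a match after rounding up does not show how 53 was calculated, and power at a difference of 0.94 depends on the σ that is not printed. The 34% is one conditional reading beside the 80% reading.

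It can also be said that the article calls the trial a pilot (Objectives, Eligibility Criteria) and exploratory (Trial Design). That lowers the weight of a possible power shortfall. It does not excuse a power statement that cannot be checked against its own inputs. Nor is this a detail that an article leaves to a fuller document, because the calculation is set out here and does not close.

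**Conclusion.** The paragraph is wrong as written, and the documents cannot settle which figure is at fault. There are two main readings, and each requires a printed figure to change.

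- If d = 0.3 is the standardised difference, 80% power needs about 175 evaluable per arm, and 53 per arm gives about 34% (37% if all 59 are evaluable). The stated power is then wrong.
- If σ was about 1.71 to 1.73, 53 per arm and 80% power are right, but the standardised difference is about 0.54 to 0.55, and d = 0.3 is wrong as an effect size.

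If 0.3 means something else, 53 has no stated dispersion behind it and cannot be checked. In every case one symbol stands for two quantities, 0.3 and 10%.

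The figures assume a two-sided 5% comparison of two means with equal arms, as printed. The normal approximation and the t-test agree to within one percentage point of power. The inflation from 53 to 59 per arm is unaffected.

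**What to change.** Rewrite the Sample Size paragraph and leave recruitment at 118.

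- Print the σ and the standardised difference actually used, and show that they lead to 53.
- If σ was about 1.72, replace d = 0.3 with a standardised difference of about 0.55.
- If 0.3 is the intended standardised difference, replace the 80% power with about 34% at 53 evaluable per arm, and state that 80% power holds only for differences of about 0.54 SD or more.
- Use a separate symbol for the 10% drop-out rate.

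The cost is one paragraph of text and no extra patients. The stated power or the detectable difference may look less favourable afterwards.
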